## Abstract

**Background:**

The i♥rhythm project is a mobile health adaptation of interpersonal and social rhythm therapy designed to promote healthy sleep and behavioral rhythms among 5-8-year olds during summer for the prevention of accelerated summer weight gain.

**Objective:**

This pilot study will examine the feasibility, acceptability, and preliminary efficacy of the i♥rhythm intervention. This will ensure that the research protocol and procedures work as desired and are acceptable to families in preparation for the fully powered randomized controlled trial. The proposed study will examine the willingness of participants to participate in the intervention and determine whether modifications to the intervention, procedures, and measures are needed before conducting a fully powered study. We will assess our ability to (1) recruit, consent, and retain participants; (2) deliver the intervention; (3) implement the study and assessment procedures; (4) assess the reliability of the proposed measures; and (5) assess the acceptability of the intervention and assessment protocol.

**Methods:**

This study will employ a single-blinded 2-group randomized control design (treatment and no-treatment control) with randomization occurring after baseline (Time 0) and 3 additional evaluation periods (postintervention [Time 1], and 9 months [Time 2] and 12 months after intervention [Time 3]). A sample of 40 parent-child dyads will be recruited.

**Results:**

This study was approved by the institutional review board of Baylor College of Medicine (H-47369). Recruitment began in March 2021. As of March 2022, data collection and recruitment are ongoing.

**Conclusions:**

This study will address the role of sleep and circadian rhythms in the prevention of accelerated summer weight gain and assess the intervention’s effects on the long-term prevention of child obesity.

**Trial Registration:**

ClinicalTrials.gov NCT04445740; https://clinicaltrials.gov/ct2/show/NCT04445740.

**International Registered Report Identifier (IRRID):**

DERR1-10.2196/37002

## Introduction

Accelerated summer weight gain has been shown to contribute to increasing rates of overweight and obesity during elementary school [1,2]. However, school-summer differences in diet, physical activity, and sedentary behavior have not been associated with differences in the rate of BMI change during the school year and summer [3]. While summertime interventions targeting children’s physical activity during summer have been demonstrated to increase physical activity levels, their impact on children’s BMI outcomes remains less clear [4]. These findings underscore the need to consider novel determinants of accelerated summer weight gain in the designs of interventions [5].

The transition from the school year to summer represents times during which students experience changes in their behavioral rhythms and routines [6]. Circadian rhythm misalignment has been implicated as a risk factor in obesity onset [7-9] and may be part of this seasonal/school-year variation. Specifically, shifts in the daily behavioral rhythms of sleep [10-13] are associated with increased adiposity, mediated through subsequent desynchronization between the central circadian clock in the suprachiasmatic nucleus and peripheral clocks [7,9,14]. School provides a natural structure for families, requiring children to follow a relatively consistent routine, promoting consistent sleep-wake patterns, mealtimes, and physical activity patterns. During out-of-school times such as summer vacation, bedtime is often later [15-17]. Later sleep timing may contribute to shortened sleep duration among younger elementary school-age children who fail to compensate with a delayed wake time [15]. Both shortened and more variable sleep duration have been associated with increased obesity risk in elementary-age children [10,12,18,19].

Differences in children’s sleep, physical activity, and light exposure during the school year and summer were related to children going to bed 1.5 hours later in summer compared with the school year [17]. Having a later sleep midpoint during summer predicted greater increases in BMI during summer, but was not associated with a change in BMI during the school year. Additionally, greater levels of outdoor light exposure during the school year predicted smaller increases in BMI during the school year. Interestingly, sleep duration, day-to-day variability in the midpoint between sleep onset and offset, physical activity levels, and sedentary behavior were not associated with a change in BMI during the school year or summer [17]. However, the importance of sleep timing and light exposure to changes in children’s BMI during the school year and summer suggests the potential importance of circadian rhythm–related behaviors, such as sleep timing and light exposure, for promoting a healthy weight status in children. To our knowledge, there is a lack of interventions designed to promote healthy sleep and behavioral rhythms among children during summer.

Interpersonal and social rhythm therapy (IPSRT) is an evidence-based treatment for bipolar disorder that promotes regularity of behavioral rhythms, such as sleep-wake cycles, meal times, and physical activity, to prevent desynchronization of endogenous circadian rhythms that precede depressive and manic episodes [20]. Behavioral rhythms are self-monitored, and behavioral strategies are used to increase the consistency of routines [20-22]. IPSRT is based on social zeitgeber theory [23], which posits that work schedules, family life, and community act as cues affecting circadian entrainment. These influences can be characterized as social demands, which influence circadian entrainment or the synchronization of circadian rhythms through “gating” exposure to the light-dark cycle and influencing the timing of behavioral rhythms [24]. It is hypothesized that a change in social demands such as the transition from the school year to the summer environment may lead to a change in behavioral rhythms [25,26], such as the timing of sleep, meals, and evening screen time, resulting in a change in exposure to morning and evening light as well as increased day-to-day variability. These changes in exposure may result in circadian misalignment, thus predisposing individuals to obesity [25-27]. Adapting IPSRT to promote healthy sleep and behavioral rhythms in children may offer promise as a method to prevent accelerated summer weight gain among children during summer.

The i♥rhythm project is an adaptation of IPSRT. It aims to promote healthy sleep habits and stable behavioral rhythms during summer for the prevention of obesity in young elementary school-age children. The intervention is designed to be delivered via mobile health (mHealth) technologies to better reach parents during summer. Parents receive information about the importance of healthy sleep and consistent behavioral rhythms and are guided through a series of steps to develop plans to support their child’s healthy sleep habits and stable behavioral rhythms during summer. This paper describes the research design, methods, and data analysis plan for an ongoing randomized controlled trial designed to evaluate the feasibility, acceptability, and preliminary efficacy of the i♥rhythm project to prevent accelerated summer weight gain. It is hypothesized that a priori feasibility criteria will be met and the intervention and assessment protocol will be found to be acceptable by participants (feasibility and acceptability criteria are outlined in detail in the “Methods” section). As this is a feasibility study, it is not powered to detect differences between groups; however, we anticipate that participants in the treatment condition will have an earlier circadian phase as measured by dim light melatonin onset (DLMO) and changes in BMI will be in the expected direction. Specifically, after intervention, participants in the i♥rhythm project will demonstrate earlier DLMOs and smaller increases in BMI compared with participants in the control condition.

## Methods

### Study Design

Figure 1 illustrates the study timeline. We will employ a single-blind 2-group randomized control design (treatment and control) with randomization occurring after baseline in the spring/end of the school year (Time 0) and 3 postintervention evaluation periods: immediately after intervention (end of summer; Time 1), 9 months after intervention (spring; Time 2), and 12 months after intervention (summer; Time 3). Because the primary objective of the i♥rhythm project is to prevent children from beginning a trajectory toward overweight/obesity in elementary school, we will explore the impact of the intervention on change in BMI during the following summer (Times 2-3), identifying whether a maintenance intervention is needed. Following the intervention (Time 1) and final data assessment (Time 3), qualitative interviews will explore the acceptability of the intervention, barriers, facilitators, difficulties with study procedures, maintenance of improvements, and self-efficacy to maintain improvements.

**Figure 1 figure1:**
[figure not shown]
Study timeline.

### Participants

The i♥rhythm project is intended for children between the ages of 5 and 8 and their parents. This age group was selected because by using group-based trajectory modeling, we identified that about 19% of children began a trajectory toward overweight/obesity beginning the summer after kindergarten and the summer after second grade [28]. To be eligible for participation parent-child dyads must meet the following criteria: (1) index child must be between 5 and 8 years old and enrolled in kindergarten, first, or second grades; (2) index child must have a BMI >50th percentile (BMI>50th percentile in elementary school is associated with greater risk of transitioning to an unhealthy weight status or obesity at age 12 [29]); (3) parent identifies as a daily user of social media and willing to engage in a social media intervention on Facebook; (4) parent owns a smartphone; (5) parent is comfortable participating in the intervention and responding to questionnaires in English; (6) families must live within the Greater Houston area and be willing to attend 4 in-person assessment visits at the Children’s Nutrition Research Center (CNRC). Exclusion criteria include parent report that the index child (1) has been diagnosed with a chronic medical condition that influences sleep, eating behaviors, weight status, or circadian rhythms; (2) is being treated with a medication or supplement known to affect sleep, such as melatonin or stimulants; (3) has been retained 2 or more grades for academic reasons or has intellectual difficulties that would influence their ability to complete questionnaires or participate in interviews; (4) has participated in an obesity prevention or obesity treatment program in the last 6 months.

### Sample Size

Sample size recommendations for pilot studies vary, with some recommending 30 per group and others suggesting a few as 12 per group [30-33]. Our intention at the outset of the trial was to recruit 30 parent-child dyads per group. To account for an attrition rate of up to 20% [34,35] we aimed to recruit 36 parent-child dyads per group. The trial was intended to begin in the Spring of 2020, but due to the COVID-19 pandemic, the start was delayed by 1 year. Because of a delay in the trial start date, our recruitment goals were amended. Given the shortened study timeline, the new recruitment goal was to recruit a sample size of 16 parent-child dyads per group. Accounting for an attrition rate of up to 20%, this established a new recruitment target of 20 parent-child dyads per group (40 total parent-child dyads).

### Procedures

#### Recruitment

Recruitment began in March 2021. Because this study will examine the feasibility of a summertime intervention, parent-child dyads will be recruited only in the spring school semester, according to the Houston Independent School District Academic Calendar (approximately February through May). Participants will be recruited through a volunteer database and Facebook advertisements targeting families in the local Houston, Texas area. Data collection will not occur within 1 week following the transition to Daylight Saving Time [36].

#### Eligibility Assessment and Consent

Interested families will complete an online eligibility questionnaire that is accessed either through an email or a Facebook advertisement. To minimize in-person visits during the pandemic, families that completed the online questionnaire and were eligible will attend a virtual screening visit using Zoom to confirm their eligibility. Before the virtual visit, families will be provided a copy of the consent form and a video with instructions for collecting height and weight in the home [37]. If a digital scale or a measuring tape/ruler is not available in the home, one will be mailed to families. On the Zoom call, informed consent will be obtained, and parents will complete the at-home assessment of height and weight to verify that the child’s BMI is >50th percentile. Eligible families will then be scheduled for a baseline assessment at the laboratory that will take place between April and the commencement of the summer break from school. Time 1 assessment will begin following the conclusion of the 5-week intervention with the goal of completing all assessments during the remaining summer break before returning to school. Time 2 and 3 assessments will occur 9 months (end of the school year) and 12 months (end of summer) after completion of the intervention, respectively (Figure 1 and Table 1).

**Table 1 table1:** Measurement timeline.

		Time 0	Intervention	Time 1	Time 2	Time 3

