Considering the developmental abilities of children aged 5-8, parents are considered the primary agent of change, though child viewing of the videos is encouraged. Session links will be emailed to participants and posted to a private Facebook group on Sunday mornings beginning the first week of summer break. The private Facebook group serves to promote social support for parents and to provide parents access to additional resources through daily (Monday-Friday) posts (Table 2 contains an example week). The Facebook group will be administered and monitored daily by research staff who assisted in the development of the intervention. The PI ([name]) will meet weekly with the intervention delivery team to ensure the intervention is delivered according to protocol. To ensure the PI remains blinded, no participant identifying information will be used in these meetings.

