#### Control

Control participants will not receive an intervention and will only participate in Time 0, 1, 3, and 4 assessments as outlined in Table 1.

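### Times 2 and 3 are counted from completion of an early-summer intervention, so taken literally Time 3 falls in mid-summer and the Times 2-3 interval does not isolate the following summer

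*Protocol article*

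**What the plan says.** All references are to the protocol article.

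- **Start of the intervention** (Experimental Condition): session links are emailed and "posted to a private Facebook group on Sunday mornings beginning the first week of summer break".
- **Length and Time 1** (Eligibility Assessment and Consent): "Time 1 assessment will begin following the conclusion of the 5-week intervention", with the aim of finishing Time 1 before school resumes.
- **Times 2 and 3** (same section): "Time 2 and 3 assessments will occur 9 months (end of the school year) and 12 months (end of summer) after completion of the intervention".
- **Study Design** gives the same offsets with looser labels: "9 months after intervention (spring; Time 2), and 12 months after intervention (summer; Time 3"). It describes Time 1 as "immediately after intervention (end of summer; Time 1").
- **Use of the interval** (Study Design): "we will explore the impact of the intervention on change in BMI during the following summer (Times 2-3"), in order to judge whether a maintenance intervention is needed.
- **Control arm** (Control): controls "will only participate in Time 0, 1, 3, and 4 assessments as outlined in Table 1". Table 1 has Times 0, 1, 2 and 3 and no Time 4.

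**The concern.** The month offsets and the season labels for Times 2 and 3 do not describe the same dates. The text treats completion of the intervention as if it were the end of summer, but the intervention is complete well before that. A site could schedule Time 3 in early July or in August and comply with part of the text either way.

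The choice affects what is measured. The Introduction reports that a later sleep midpoint predicted BMI gain in summer but not in the school year. An interval that mixes several weeks of school with part of a summer is therefore a different quantity from summer BMI change. Randomisation would keep the arms comparable over that interval, but the comparison would no longer answer the stated question about the following summer.

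The control-arm line adds a smaller problem: it names a visit that does not exist and leaves out one that does.

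**Working it through.** **Inputs from the article.** Intervention start: first week of summer break (taken as day 0). Length: 5 weeks = 35 days. Offsets: 9 and 12 months after completion.

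**Assumptions, not in the article.** The break starts between 23 May and 13 June, on the same date in both years, and lasts 10-12 weeks.

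**1. Offsets counted from completion, as written**
- Completion = day 35 of the break.
- Time 3 = completion + 12 months = about day 35 of the next break (27 June to 18 July). School resumes 10 - 5 = 5 to 12 - 5 = 7 weeks later.
- Time 2 is three months earlier, about 91 days: 91 - 35 = 56 days, or about 8 weeks, before the next break (27 March to 18 April).
- School share of Times 2-3 = 56/91 = 62%; summer share = 35/91 = 38%. This hardly depends on the break date.
- Share of the break covered = 35/84 = 42% (12 weeks) to 35/70 = 50% (10 weeks).

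The end-of-summer label for Time 3 is not reproduced from the stated anchor.

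**2. Allowing for the length of an assessment**

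Under Data Collection, the actigraph is worn for 8 days and the laboratory visit, where BMI is measured, follows 1-2 days later. If wear starts on the nominal date (an assumption), BMI is measured 8 + 1 = 9 to 8 + 2 = 10 days later at both visits.
- Summer days in the interval = 35 + 9 = 44 to 35 + 10 = 45.
- Summer share = 44/91 = 48% to 45/91 = 49%.
- Share of the break covered = 44/84 = 52% to 45/70 = 64%.

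**3. Same offsets counted from a later anchor** (break starting 6 June)

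| Anchor, weeks into break | Time 2 | Time 3 | School days / total | School share |
|---|---|---|---|---|
| 5 | 11 April | 11 July | 56/91 | 62% |
| 6 | 18 April | 18 July | 49/91 | 54% |
| 7 | 25 April | 25 July | 42/91 | 46% |
| 8 | 1 May | 1 August | 36/92 | 39% |
| 10 | 15 May | 15 August | 22/92 | 24% |
| 11 | 22 May | 22 August | 15/92 | 16% |

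For an anchor at the end of the break, over all the assumed starts and lengths, Time 2 falls about 1-3 weeks before the next break, Time 3 falls at its end, and school makes up about 9-24% of the interval. Both labels then fit.

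**4. Control-arm visits, side by side**
- Control: Times 0, 1, 3 and 4.
- Table 1: Times 0, 1, 2 and 3, with BMI ticked at each and no restriction by arm.
- Participants: every family must be willing to attend 4 in-person visits.
- Data Analysis Plan: Times 0, 1, 2 and 3 modelled in both groups, with a group-by-time interaction.

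Three places agree on four visits for everyone, and two of them number the visits 0 to 3. The Control line is the odd one out.

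**The case against.** The strongest reply is that 9 and 12 months are nominal. Time 1 is itself labelled end of summer, may run through the remaining break, and according to Limitations ended in August 2021. Results expects data collection to finish in September 2023, which is compatible with end-of-summer Time 3 visits for families recruited in 2022. On that reading the intended schedule is sound. This stands as an account of what was probably meant, but the text names completion of the intervention as the anchor, and from that anchor the end-of-summer label fails.

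Three stronger readings are tempting, and the article does not support them.

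- *Time 2 cannot be the end of the school year.* Baseline runs from April to the start of the break, and Study Design calls that period spring or end of the school year. For most of the assumed start dates a literal Time 2 falls inside that window. The mismatch is clear for Time 3 and mild for Time 2.
- *The interval is 38% summer, as a fixed figure.* That share puts the BMI measurement exactly on the nominal day. With the assessment lead-in it is close to half.
- *Controls are to skip Time 2, so no between-arm comparison exists over Times 2-3.* The Control line defers to Table 1, and Table 1, the four-visit requirement and the analysis model all include controls at Time 2. It is a numbering slip.

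Figure 1, the study timeline, is not shown and may already give calendar windows. The aim affected is also exploratory: feasibility is the primary outcome, and the pilot is stated not to be powered for group differences.

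**Conclusion.** The point holds as a mismatch between anchor and label. Followed literally, the rule puts Time 3 about 5 weeks into the next break, and about 38-49% of the Times 2-3 interval is summer, depending on when the BMI visit falls. It would observe roughly half of the break: 42-50% on the nominal dates, 52-64% with the visit 9-10 days later. That does not isolate BMI change over the following summer. Counted from an end-of-break Time 1 visit, the same offsets give an interval that is 76-91% summer (100 minus 24 and 100 minus 9), so the design can deliver what Study Design promises once the anchor is corrected.

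The shares rest on a literal reading of the anchor. The coverage and end-of-break figures also rest on the assumed break length of 10-12 weeks. The point deserves correction because a stated scheduling rule yields the wrong interval for a stated aim, but it does not threaten the pilot's primary feasibility objectives. The control-arm line is a separate clerical error.

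**What to change.** 1. In Eligibility Assessment and Consent, drop completion of the intervention as the anchor for Times 2 and 3. Define Time 2 as a window in the last weeks before the next summer break and Time 3 as a window in the last weeks of that break, matched where possible to each child's own Time 0 and Time 1 windows one year earlier.
2. Make Study Design agree: the same windows, any month offsets marked as approximate, and Time 1 described consistently as a visit after the 5-week intervention and before school resumes. Check Figure 1 against the result.
3. In Control, change the visit list to Times 0, 1, 2 and 3, in line with Table 1 and the Data Analysis Plan.

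The cost is wording in three sections and no added visits. Recruitment and data collection were still under way when the article was written, so clear windows could still guide scheduling.

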**Primary outcomes**						
	Recruitment goals	✓	✓			
	Intervention fidelity		✓			
	Intervention adherence		✓			
	Acceptability of assessments			✓		✓
	Treatment acceptability			✓		
	Retention		✓	✓	✓	✓
	BMI	✓		✓	✓	✓
	Dim light melatonin onset	✓		✓	✓	✓
**Secondary outcomes**						
	Sleep as assessed by actigraphy	✓		✓	✓	✓
	Body composition	✓		✓	✓	✓
	Dietary assessment	✓		✓	✓	✓
	Physical activity/inactivity	✓		✓	✓	✓
**Covariates**						
	Parent-child demographics	✓				
	General and sleep-related parenting practices	✓		✓	✓	✓
	Perceived stress (parent)	✓		✓	✓	✓
	Social support (parent)	✓		✓	✓	✓
	Child care during summer	✓		✓	✓	✓

#### Blinding

The principal investigator (PI; [name]) and statistician will be blinded to the treatment condition. The outcome assessors will not be blinded to the condition. Selection bias in the unblinded study personnel will be minimized through the randomization procedure.

